## Abstract

**Background:**

Asthma and obesity are public health problems with increasing prevalence worldwide. Clinical and epidemiologic studies have demonstrated that obese asthmatics have worse clinical control and health related quality of life (HRQL) despite an optimized medical treatment. Bariatric surgery is successful to weight-loss and improves asthma control; however, the benefits of nonsurgical interventions remain unknown.

**Methods/Design:**

This is a randomized controlled trial with 2-arms parallel. Fifty-five moderate or severe asthmatics with grade II obesity (BMI ≥ 35 kg/m^2^) under optimized medication will be randomly assigned into either weight-loss program + sham (WL + S group) or weight-loss program + exercise (WL + E group). The weight loss program will be the same for both groups including nutrition and psychological therapies (every 15 days, total of 6 sessions, 60 min each). Exercise program will include aerobic and resistance muscle training while sham treatment will include a breathing and stretching program (both programs twice a week, 3 months, 60 min each session). The primary outcome variable will be asthma clinical control. Secondary outcomes include HRQL, levels of depression and anxiety, lung function, daily life physical activity, body composition, maximal aerobic capacity, strength muscle and sleep disorders. Potential mechanism (changes in lung mechanical and airway/systemic inflammation) will also be examined to explain the benefits in both groups.

**Discussion:**

This study will bring a significant contribution to the literature evaluating the effects of exercise conditioning in a weight loss intervention in obese asthmatics as well as will evaluate possible involved mechanisms.

**Trial registration:**

NCT02188940

## Background

Asthma is a chronic respiratory disease characterized by episodes of reversible airway obstruction, chronic airway inflammation and airway hyperresponsiveness. Its symptoms include wheezing, shortness of breath, chest tightness and cough, which may resolve either spontaneously or with the administration of an appropriate treatment [1]. Asthma affects approximately 300 million people worldwide and is expected to affect an additional 100 million people by 2025 [1, 2]. The dramatic increase in the prevalence of asthma over the past few decades has occurred in conjunction with an increase in the prevalence of obesity [3, 4], a finding suggestive of a possible relationship between the two conditions. Obesity is characterized by excess fat accumulation in the body as a result of a complex interaction among genetics, dietary caloric intake and energy expenditure and is often diagnosed in adults with a BMI ≥ 30.0 kg/m^2^ [5]. Obesity also affects a large number of individuals, as more than 200 million men and nearly 300 million women are obese. The prevalence of obesity is highest in WHO Regions of America (27 % of obesity) and lowest in the WHO Regions for South East Asia (5 % of obesity) [6].

Many cross-sectional epidemiologic studies have demonstrated a relationship between asthma and obesity [7–9]. Obesity is a major risk factor for asthma, as overweight and obese subjects are 38 % and 92 % more likely to develop asthma, respectively, than patients with normal weights [10]. Additionally, obesity results in the development of a difficult-to-control asthma phenotype in which patients experience worse clinical control, poorer quality of life, reduced lung function, poor responses to corticosteroids and more psychosocial symptoms [11–14]. As obesity is a risk factor for the development of asthma, Global Initiative for asthma (GINA) 2014 [1] recommends weight loss for all obese asthmatics.

Some interventions have been considered for weight loss in obese asthmatic patients and bariatric surgery has been suggested as a means of improving asthma control, lung function and decreased medication usage [15, 16]. However, the most recent guidelines pertaining to the management of obesity recommend utilizing a comprehensive approach to weight-loss intervention focused on diet, physical activity and behaviour self-management as a first-line therapy [17].

A recent Cochrane review found only 4 randomized controlled trials (RCTs) pertaining to weight loss in the setting of asthma [18] via nonsurgical intervention. Two trials used meal replacement with a very low calorie diet [19, 20], and Dias-Junior et al. [21] combined a low calorie diet with anti-obesity drugs (orlistat and subtramine). Each of these studies observed positive effects following weight loss. The study by Scott et al. [22] was the only to include physical activity as an adjuvant treatment; the authors observed that the patients who participated in physical activity did not experience additional benefits in terms of weight loss and improvements in clinical control, although this finding may have overlooked the levels of physical activity in which these patients participated at baseline. Therefore, the Cochrane review study did not find any studies using a comprehensive approach to lifestyle intervention focused on diet, physical activity and behaviour self-management as recommended by the most recently published guidelines [17].

Recent evidence suggests that improving physical fitness among patients with asthma is important because it improves airway hyperreactivity [23], psychosocial factors [24], and health related quality of life [25], and also reduces the need for corticoid administration [23, 26]. Moreover, recent studies have also demonstrated the anti-inflammatory effects of exercise training in patients with asthma [27, 28]; these results are consistent with those of studies utilizing animal asthma models [29–31]. Additionally, improvements in physical fitness also effect the immune system in obese subjects by decreasing the activity of pro-inflammatory mediators [Interleukin (IL-6), monocyte chemotactic protein-1 (MCP-1), C-reactive protein (CRP), IL-8 and tumour necrosis factor (TNF-α)] and increasing the levels of anti-inflammatory markers and mediators (adiponectin and IL-10) [32–34]. Therefore, exercise not only plays a role in lifestyle interventions intended to facilitate weight loss in asthma but is also an intervention in and of itself.

As previously discussed, asthma and obesity are clinical conditions characterized by chronic inflammation; the effects of exercise have been evaluated in the setting of each condition but not in the setting of both diseases together. Our hypothesis is that exercise training amplifies weight loss and exerts both anti-inflammatory and immunoregulatory effects, resulting in improved clinical control and quality of life, as well as improved psychosocial symptoms and sleep disorders among obese asthmatic patients. The objective is to assess the effects of exercise training in a weight-loss program on asthma control, quality of life and psychosocial symptoms in obese patients with stable asthma.

## Methods

### Study design

This is a prospective and randomized open-label controlled trial with 2 arms and blinded assessments. Both groups will receive similar educational and weight loss interventions (composed of both nutritional and psychological therapies), but only one group will perform exercise training. The study design is depicted in Fig. 1.

**Fig. 1 Fig1:**
[figure not shown]
Study flow chart. After being included in the study, the patients will be evaluated during 3 non-consecutives visits. Each of the groups will receive the same education program and will participate in the same weight loss program* (composed of nutrition and psychological therapy); however, only one of the groups will participate in exercise training, as the remaining group will perform a sham intervention (breathing and stretching exercises). The groups will performed 24 intervention session, after which they will undergo a second evaluation utilizing the same tests as the baseline evaluation

### Study setting

The patients will be recruited from an outpatient asthma clinic at a University hospital. The Hospital Research Ethics Committee of the University of Sao Paulo approved the study, (07137512.9.0000.0068) and all patients provided written informed consent before participating. This study is registered on ClinicalTrials.gov as NCT02188940.

### Eligibility criteria

Patients between 30 and 60 years of age with class II obesity (BMI ≥ 35 kg/m^2^) and either moderate or severe persistent asthma according to the GINA criteria [1] will be eligible to participate. The subjects will have to be under medical treatment for at least 6 months and to have clinically stable disease (no hospitalizations, emergency care or medication changes for at least 30 days). The patients should will also be physically inactive as defined by the American College of Sports Medicine’s (ACSM) guidelines (less than 60 min of structured or planned physical activity per week) within the last 6 months [35]. The exclusion criteria included the following: the presence of another pulmonary disease, either cardiovascular or musculoskeletal diseases that may interfere with the patient’s evaluations or impair exercise training, active cancer, a weight change greater than 5 % within the last 6 months, taking anti-obesity drugs within the past 3 months, a history of bariatric surgery, either uncontrolled hypertension or diabetes, and the use of continuous positive airway pressure. Patients who are participating in another research protocol or are unable to understand our questionnaire, as well as smokers or ex-smokers (≥10 pack-years), pregnant women or breast feeding women, will also be excluded. The interventions will be performed between 2 medical appointments in order to avoid medication changes.

### Experimental design

The patients will be assessed before and after the interventions on 3 non-consecutive days. On day 1, anthropometric indexes, body composition, asthma symptoms and peripheral muscle strength will be assessed. On day 2, asthma clinical control will be assessed via an asthma control questionnaire (ACQ), an asthma quality of life questionnaire (AQLQ), and a hospital anxiety depression scale (HADS); sleep disorder history, lung function and exercise capacity will be also assessed. On day 3, the exhaled fraction of nitric oxide (FeNO), daily life physical activity and systemic inflammation will be measured. Following these baseline evaluations, all eligible patients will receive a 6-h educational program and will be subsequently randomly assigned into the following 2 groups: either a weight loss program (including nutritional and psychological therapy) with a sham treatment (WL + S group), or the same weight loss program with exercise (WL + E group). All patients will complete 24 treatment sessions, after which they will be reevaluated.

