#### Nutritional intervention

A nutritionist will conduct the nutritional program with visits every 2 weeks during the 3 month intervention period, for a total of 6 sessions of 60 min each for both groups. The patients will be advised to follow a hypocaloric diet in which the calorie intake of each patient will be estimated by multiplying adjusted body weight (at a BMI of 25 kg/m^2^) by 20 calories [37]. Food consumption will be evaluated using a 24-h food record, and all caloric intake, macronutrients and micronutrients will be quantified using NutWin® software (recommended dietary allowances based on a food pyramid) [38]. The patients will complete the food dairy at the beginning (1^st^ session), the middle (3^rd^ session) and the end (6^th^ session) of the sessions. During each session, the nutritionist will measure and record the patients’ weights, discuss the importance of maintaining a balanced diet, and promote appropriate daily food intake and make each patient aware of the responsibility one bears in controlling one’s weight (Table 1).

**Table 1 Tab1:** Nutritional program

No. session	Activities
1	Presentation of the group and the nutritional program
	The measurement and recording of body weights, concepts of BMI/obesity range
	A balanced food pyramid and how to complete the 24 hour food intake dairy
2	The measurement and recording of body weight
	Individualized calorie goals with dietary suggestions
	Daily food routine and portion sizes
3	The measurement and recording of body weight
	The role of carbohydrates, proteins and fats in a diet
	Choices of low-energy and nutrient-dense meals and snacks
4	The measurement and recording of body weight
	The role of vitamins and minerals
	The ideal amount of nutrient intake to lose weight and stay healthy
5	The measurement and recording of body weight
	Healthy food preparation techniques and proposals for healthy meals
	The risk of diabetes and hypertension associated with obesity (comorbidities)
6	The measurement and recording of body weight
	“Virtual restaurant” and how to read a food nutrition labels
	Careful selection of restaurants and the finalization of the nutrition program

*BMI* body mass index, *No.* number of session. The nutritional program will be performed every 15 days over 3 months for a total of 6 sessions of 60 min each

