#### Exercise training program

The exercise training program will include aerobic and resistance exercises supervised by a physiotherapist and will be offered to only one of the groups (WL + E group). The program will be performed twice a week for 3 months for a total of 24 sessions of 60 min each. In order to avoid joint discomfort and improve patient adherence to the exercise program, aerobic training will be performed on both a treadmill (Jog 700, Technogym, Italy) and either a bike (Bike 700, Technogym, Italy) or an elliptical (Syncro 700, Technogym, Italy) machine. The intensity of the aerobic training will be based on peak oxygen consumption (peak VO_2_) and monitored using each patient’s target heart rate (THR). Exercise intensity will begin with a THR of 50 to 60 % of peak VO_2_ and will be increased by 5 % every 2 weeks based on symptoms and perceived exertion, using the modified Borg scales for leg discomfort and dyspnea [40], reaching a maximum of 75 % of peak VO_2_ [41]. Each patient will receive an accelerometer in order to record daily numbers of steps during the 1^st^, 6^th^ and 12^th^ weeks to encourage an increased physical activity level. In order to complete the amount of weekly physical activity recommended by the international guidelines [35], the patients will be also advised to walk at least twice a week for 30 min and to complete a daily physical activity record. Both heart rate and the modified Borg scale [40] will be assessed during each session before exercise, every 10 min during exercise and after exercise. Peak expiratory flow (PEF) will be measured before each session, and inhaled salbutamol (200 μg) will be recommended if values < 70 % were observed. The safety of the exercise training will be monitored by quantifying PEF, blood pressure and asthma symptoms before and after each exercise session as previously described [28].

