#### Sham treatment

The breathing and stretching exercise programs will be completed only by the WL + S group; the sessions will be performed twice a week for 12 weeks and will be supervised by a physiotherapist. The breathing and exercise programs will be performed as a sham treatment as previously described [24, 28], without an intensity progression. The program will be based on Yoga’s pranayama breathing exercises, including *kapalabhati*, *uddhiyana* and *agnisara,* as previously described [43]. Briefly, every exercise will be completed in 3 sets with 2 min of exercise intercalated with 60 s of rest for a total of 30 min each session. The stretching program will consist of exercises for the following major muscle groups: trapezius, pectoralis, gluteus, hamstrings, quadriceps femur, paraspinal, latissimus dorsi and pubic adductors. The exercises will be completed in 2 sets of 10 s each for a total of 30 min each session. The safety of these exercises will be monitored in the same way as the exercise training. The breathing and stretching exercises will be included as a sham intervention in the WL + S group in order to minimize the differences in the numbers of hospital visits and the amounts of patient attention between the two groups, not to induce respiratory breathing training benefits.

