#### Statistical analysis

An intention-to-threat analysis will be used to preserve the effects of group allocation and provide an assessment of the practical impact of the treatment [74], as recommended by the CONSORT statement [75]. The normality of continuous outcomes will be assessed via the Kolmogorov-Smirnov test. Comparisons of the initial and final data will be analyzed via a two-way repeated-measures analysis of variance, and the categorical outcomes, via the *χ*^2^ test. A partial correlation will be used to test the effects of airway and systemic inflammation as mediators. P values ≤ 0.05 will be considered statistically significant. The statistical analysis will be blinded to the treatment allocation and will be performed using specific software (SigmaStat 3.5, Systat Software Inc.).

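### The final evaluation is tied to completing 24 sessions, with no fixed time point and no stated evaluation of patients who stop early, which puts the intention-to-treat aim at risk

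*Protocol article*

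**What the plan says.** The Experimental design section states "All patients will complete 24 treatment sessions, after which they will be reevaluated". The legend of Fig. 1 repeats the rule: "The groups will performed 24 intervention session, after which they will undergo a second evaluation". Experimental design also says, more generally, "The patients will be assessed before and after the interventions on 3 non-consecutive days". The primary outcome is the change in ACQ after the intervention, and no ACQ is described between the baseline and final evaluations.

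The programmes have a nominal calendar length:

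- Exercise training program: "The program will be performed twice a week for 3 months for a total of 24 sessions of 60 min each".
- Sham treatment: "the sessions will be performed twice a week for 12 weeks".
- Nutritional intervention: "visits every 2 weeks during the 3 month intervention period". The behavioural therapy follows the same pattern.

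Eligibility criteria adds a calendar limit: "The interventions will be performed between 2 medical appointments in order to avoid medication changes". The interval between those appointments is not given.

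On analysis, the Statistical analysis section says "An intention-to-threat analysis will be used to preserve the effects of group allocation" (an evident slip for intention to treat). The Sample size section allows for up to 20 % loss to follow-up.

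**The concern.** An intention-to-treat comparison needs an outcome on as many randomised patients as possible, at a comparable time. Here the one written trigger for the only post-baseline ACQ is an event that depends on attendance. Attendance arises after randomisation and may differ between progressive aerobic and resistance training and a breathing and stretching programme without progression.

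Two things are at stake. The first is completeness: the trigger presumes that everyone finishes, while the sample size section expects that some patients will be lost. The second is timing: the ACQ refers to the last week, so its date decides which week of the patient's course is measured. A late evaluation lies further from the end of the nutrition and psychology sessions if those keep to their own schedule. It could also fall after the second medical appointment, since the appointment rule names the interventions and not the re-evaluation that follows them.

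**Working it through.** **Inputs from the article.** 24 sessions; 2 per week; nominal 12 weeks or 3 months; 55 patients; up to 20 % loss; target difference 0.5 ACQ points. **Assumed, because the article gives no figure:** attendance per session, non-completion by arm, and outcomes in non-completers.

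**1. The article's own schedule.** 24 sessions / 2 per week = 12 weeks. The session count and the calendar agree, but only if no session is missed.

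**2. If missed sessions are made up.** Mean week of the 24th attended session = 12 / attendance. The 5th to 95th percentile comes from a negative binomial distribution with independent attendance at each slot.

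| Assumed attendance | Mean week of session 24 | 5th–95th percentile (weeks) |
|---|---|---|
| 100 % | 12 / 1.0 = 12.0 | – |
| 90 % | 12 / 0.9 = 13.3 | 12.0–15.0 |
| 80 % | 12 / 0.8 = 15.0 | 13.0–17.5 |
| 70 % | 12 / 0.7 = 17.1 | 14.5–20.5 |

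**3. If missed sessions are not made up.** The probability of attending all 24 is p^24:

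- 0.99^24 = 0.79
- 0.95^24 = 0.29
- 0.90^24 = 0.08
- 0.80^24 = 0.005

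Read literally, the trigger would then be reached by a minority even at 95 % attendance.

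Steps 2 and 3 are alternatives. A given missed session either delays the evaluation or leaves the patient short of the trigger, not both.

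**4. Patients at issue.** 20 % of 55 = 11, leaving 44 evaluated if all the allowed loss occurs. The article does not say how much of that loss, if any, the session rule would cause.

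**5. Illustrations only: what analysing completers alone could do.**

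- *Unequal non-completion.* If non-completers do worse by D points in both arms, the completers-only difference is off by D × (pE − pS), where pE and pS are the non-completion proportions with exercise and sham. With an assumed 30 % against 10 % and D of 0.5 to 1.0: 0.5 × 0.20 = 0.10 and 1.0 × 0.20 = 0.20 points. That is 20 to 40 % of the 0.5-point target, in favour of exercise. Swapping the proportions reverses the sign. Equal proportions with the same D give zero.
- *Equal non-completion of 20 %, with a different benefit in non-completers.* If completers differ by 0.5 between arms and non-completers by e, the effect in all randomised is 0.8 × 0.5 + 0.2 × e. This is 0.40 for e = 0, 0.45 for e = 0.25 and 0.50 for e = 0.5, so a completers-only estimate would overstate it by 0 to 0.10 points.

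**The case against.** The session sentence sits in a paragraph that walks through the planned sequence, and it can be read as a description of the intended course rather than as an eligibility rule for the final visit. The general statement that patients are assessed before and after the interventions carries no completion condition. The programmes have a 3-month or 12-week length, and the two-appointment limit restricts how late session 24 can fall. The sham arm is also supervised by a physiotherapist, twice weekly, and was chosen to even out visits and attention, so nothing in the article predicts a gap in completion between the arms. A condensed article may leave visit windows and make-up sessions to a fuller protocol.

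Much of this stands. In particular, these stronger readings are not supported:

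- A reader might infer that non-completers get no outcome by design. No sentence says so; the article is silent on them.
- A reader might infer that slow attenders are necessarily measured later. That needs make-up sessions, which the article does not mention.
- A reader might infer that evaluation after a medication change is built in. It is possible, but the appointment interval is not given, so it is not shown.

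The stated rule itself remains. The article does not merely omit a window. In two places it fixes the time of the final evaluation by session count, and that choice agrees with the calendar only at full attendance. The nominal programme length dates the programme, not the evaluation.

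**Conclusion.** The point holds as a weakness in a stated rule. The final evaluation follows 24 completed sessions, without a fixed time and without a stated evaluation of patients who stop. That puts the intention-to-treat aim at risk. To say that it defeats the aim would go too far, since the analysis plan does not restrict itself to completers and nothing bars non-completers from evaluation.

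The size cannot be established from the document. Under assumed attendance of 90 % or 80 % with make-up sessions, the mean delay is 1.3 or 3.0 weeks (13.3 − 12 and 15.0 − 12). Without make-up sessions, the share reaching the trigger depends steeply on attendance. The figures of 0.10 to 0.20 and 0 to 0.10 ACQ points are illustrations. They rest on invented non-completion rates and outcomes and on a completers-only analysis that the article does not announce. The bias could be zero or run either way. The change is worth making because it is cheap and removes the ambiguity.

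**What to change.** Replace the session-count trigger, in Experimental design and in the Fig. 1 legend, with a calendar rule:

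- Every randomised patient is re-evaluated in a stated window around the article's own 3-month intervention period, whatever the number of sessions attended.
- The window is counted from randomisation, or from a planned start date that is also set for patients who never begin. Counting from the first attended session would leave those patients without a date.
- The evaluation falls, where possible, before the second medical appointment named in Eligibility criteria. The window must leave room for the three non-consecutive assessment days.
- Patients who stop treatment are invited to the same evaluation, with the ACQ as the minimum data set.
- Sessions attended are recorded as adherence data.

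The cost is a sentence or two and a visit-window rule. No test is added and no treatment changes. The small downside is that some patients will be measured with fewer than 24 sessions, so the estimate is the effect of assignment rather than of the full programme, which is what the intention-to-treat commitment asks for.
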